# A feasibility study investigating the acceptability and design of a multicentre randomised controlled trial of needle fasciotomy versus limited fasciectomy for the treatment of Dupuytren’s contractures of the fingers (HAND-1): study protocol for a randomised controlled trial

**DOI:** 10.1186/s13063-017-2127-9

**Published:** 2017-08-25

**Keywords:** Dupuytren’s contracture, Needle fasciotomy, Limited fasciectomy, Randomised controlled trial, Feasibility, Patient-reported outcome measure

## Abstract

**Background:**

Dupuytren’s contractures are fibrous cords under the skin of the palm of the hand. The contractures are painless but cause one or more fingers to curl into the palm, resulting in loss of function. Standard treatment within the NHS is surgery to remove (fasciectomy) or divide (fasciotomy) the contractures, and the treatment offered is frequently determined by surgeon preference. This study aims to determine the feasibility of conducting a large, multicentre randomised controlled trial to assess the clinical and cost-effectiveness of needle fasciotomy versus limited fasciectomy for the treatment of Dupuytren’s contracture.

**Methods/design:**

HAND-1 is a parallel, two-arm, multicentre, randomised feasibility trial. Eligible patients aged 18 years or over who have one or more fingers with a Dupuytren’s contracture of more than 30° in the metacarpophalangeal (MCP) and/or proximal interphalangeal (PIP) joints, well-defined cord(s) causing contracture, and have not undergone previous surgery for Dupuytren’s on the same hand will be randomised (1:1) to treatment with either needle fasciotomy or limited fasciectomy. Participants will be followed-up for up to 6 months post surgery. Feasibility outcomes include number of patients screened, consented and randomised, adherence with treatment, completion of follow-up and identification of an appropriate patient-reported outcome measure (PROM) to use as primary outcome for a main trial. Embedded qualitative research, incorporating a QuinteT Recruitment Intervention, will focus on understanding and optimising the recruitment process, and exploring patients’ experiences of trial participation and the interventions.

**Discussion:**

This study will assess whether a large multicentre trial comparing the clinical and cost-effectiveness of needle fasciotomy and limited fasciectomy for the treatment of Dupuytren’s contractures is feasible, and if so will provide data to inform its design and successful conduct.

**Trial registration:**

International Standard Registered Clinical/soCial sTudy Number: ISRCTN11164292. Registered on 28 August 2015.

**Electronic supplementary material:**

The online version of this article (doi:10.1186/s13063-017-2127-9) contains supplementary material, which is available to authorized users.

## Background

Dupuytren’s contractures are fibrous cords under the skin of the palm of the hand which typically occur in men and women over 50 years of age. They have a strong genetic tendency [1] and an increased incidence associated with diabetes and epilepsy [2]. The contractures are painless but cause one or more fingers to gradually curl into the palm, resulting in loss of hand function. This can lead to loss of dexterity for day-to-day tasks such as washing, grooming and shaking hands. It becomes increasingly difficult to put on a glove, hold large objects or put the hand in a pocket. Other difficulties experienced are diverse and patient dependent, and can include computer use, baking, piano playing, carpentry, gardening, and sports such as cycling, golf and tennis [3–5].

The standard treatment is surgery to remove (fasciectomy) or divide (fasciotomy) the Dupuytren’s contractures, allowing the finger to straighten better. However, this does not cure the condition, the finger may not come fully straight and recurrent contractures may require further surgery. In 2010–2011 it was estimated that the total cost of Dupuytren’s contractures procedures in England was more than £41 million with increasing rates of primary and revision procedures [6]. Increased longevity in an ageing population may cause a 77% increase in demand for treatment by 2030 [7].

There are no agreed criteria for choice of surgical treatment of Dupuytren’s contractures, but guidelines have been produced for one treatment, ‘needle fasciotomy’ (NF) [8]. The most common operation currently in the UK is ‘limited fasciectomy’ (LF), in which the fibrous cords preventing the finger from straightening are cut out of the hand through a long skin incision. This procedure is done under general or regional anaesthesia in an operating theatre, typically as a day-case admission and has a 4–6-week recovery period. Around 13,000 LFs were carried out in England in 2014–2015 [9]. A common alternative treatment is NF. In this procedure the fibrous cords preventing the finger(s) from straightening are divided with the sharp tip of a hypodermic needle which is passed through the skin without the need for a skin incision. It can be done in an outpatient clinic room and has a 1–2-week recovery period. Around 1300 NFs were recorded in UK Hospital Episode Statistics during 2014–2015, although this may be an underestimate if procedures performed in outpatient rooms are under-recorded [9].

In comparison to LF, NF is likely to be less expensive for health services, less disruptive for patients, and potentially carries a lower risk of complications that restrict hand function (temporarily or permanently) after the surgery [10]. Contractures can reform in the fingers that have been operated on after either treatment, causing the finger to bend up into the palm again, but recurrence occurs earlier and more frequently with NF, and may result in a need for further treatment [11]. There are three subtypes of Dupuytren’s contractures, those which affect the metacarpophalangeal (MCP) joint alone, the proximal interphalangeal (PIP) joint alone, or both the MCP and PIP joints. Both procedures can successfully straighten fingers with a Dupuytren’s contracture involving only the MCP joint. However, fingers with contractures involving the PIP joint cannot always be fully straightened with surgery, though LF is more successful and allows for the option of a PIP joint capsule release, if necessary.

There is no high-quality evidence comparing surgical treatments for Dupuytren’s contracture. One systematic review in 2010 found only five randomised or pseudo-randomised trials evaluating the surgical treatment of Dupuytren’s contracture [12], and a subsequent Cochrane systematic review found insufficient evidence to show the relative superiority of different surgical procedures (including NF versus fasciectomy) [13]. Although one small randomised controlled trial (RCT) comparing NF with LF showed a higher recurrence rate after NF at 5 years [11], it had methodological weaknesses, resulting in high risks of attrition, performance and detection bias [13], and did not rigorously compare hand function. Furthermore, recurrence should not be considered as indicating failure of the procedure, as it may not be sufficiently severe to warrant ‘revision surgery’ and may be managed by a further NF, with minimal inconvenience to the patient [14]. Also NF is cheaper and has a shorter recovery period than LF [10], and may produce as good hand function at 1- and 5-year follow-up [15].

Existing studies comparing NF with LF have a number of limitations; most importantly, high risk of performance and detection biases and the use of angular measurements of finger straightness and recurrence as primary outcomes rather than a patient-reported outcome measure (PROM) or an assessment of hand function. Also, none assessed the cost of treatments to either providers or patients, and none rigorously compared the outcomes of NF with LF in each of the three subtypes of Dupuytren’s contracture. The subtype, which only affects the MCP joint (40% of all contractures), is most likely to correct successfully with NF with the least risk of damage to the digital nerves and tendons [10, 11]. Surgeons are most comfortable treating this subtype by NF [16] and it may be a specific subgroup for which NF provides equivalent or better outcomes than LF.

Although function is the main problem for patients with Dupuytren’s contracture, there is no consensus about the most appropriate PROMs to assess the outcome of treatment. Most PROMs used in hand surgery are not specific to this condition. Thirteen small studies (four retrospective and six prospective cohort and three RCTs) have used PROMs as an outcome measure for Dupuytren’s contracture [17]. They used the DASH (11 studies), the QuickDASH, Part 2 of the Patient Evaluation Measure (PEM) and the Unité Rhumatologique des Affections de la Main (URAM) (one study each). Although improvements in hand function have been recorded with all after surgery, the minimal clinically important difference (MCID) for patients with Dupuytren’s contracture has only been calculated for the URAM, which may not adequately assess loss of hand function with Dupuytren’s contracture [5].

The lack of well-designed and well-conducted trials means that the choice of treatment for Dupuytren’s contractures of the fingers mainly depends on surgeon and patient preference. A survey of 116 hand surgeons showed marked variations in treatments advised for Dupuytren’s contractures [16]. The same surgeons reported that the most important research question about surgical treatment was a comparison of NF with LF. This is also an important question for patients. A recent survey [5] of 110 patients awaiting surgery found that the most important factors in deciding which treatment to undergo were recurrence (38%), surgeon guidance (37%) and speed of recovery following surgery (25%). There is an urgent need for robust evidence to guide decision-making.

In summary, a high-quality definitive trial comparing the outcomes and costs of NF with LF in patients with Dupuytren’s contracture of the MCP joint and/or PIP joint is needed. This study aims to assess the feasibility of a large multicentre trial, and to inform its design and conduct, including providing information about numbers of eligible patients, recruitment and randomisation, completion of follow-up, selection of appropriate outcome measures, and sample size.

### Objectives

The objectives of the study are to:Define the eligibility criteria for a future, definitive randomised trial comparing NF with LFEstimate the proportion of referred NHS patients with Dupuytren’s contractures who meet these eligibility criteriaDetermine the willingness of surgeons to recruit patients with different patterns of Dupuytren’s contractures of the fingersEstimate the proportion of eligible patients who consent to randomisationAssess and optimise the recruitment process and patient pathway using a QuinteT Recruitment Intervention (QRI) [18]Estimate follow-up and outcome completion ratesEvaluate outcomes for use as primary and secondary outcomes in the definitive studyAssess and compare validity and reproducibility of two methods of measurement of finger straightness which can be performed by a research assistantDetermine standard practice and equipment for clinic room provision of treatmentAssess the relationship between angular measurements of the finger deformity and patients’ reported outcomesEvaluate the utility and acceptability of health resource use questionnaires to assess the impact of care on health service use and productivityAssess patient and staff views on trial conduct, trial participation, and acceptability of interventions using qualitative research methodsCalculate the sample size required for a definitive study

## Methods/design

The HAND-1 study is a parallel, two-arm, randomised feasibility trial with participants individually allocated on a 1:1 ratio to treatment with either LF in an operating theatre, or NF in a clinic room. Participants will be followed up for up to 6 months post treatment. Embedded qualitative research incorporating a QRI [18] will focus on understanding and optimising the process of recruiting to the trial, and explore patients’ experiences of trial participation and the interventions. Audio-recordings of recruitment consultations will be a key method used to understand the recruitment process, along with regular monitoring of screening logs and interviews with trial staff and patients.

Flow of participants through the study is summarised in Fig. 1.

**Fig. 1 Fig1:**
[figure not shown]
Trial flow diagram

The HAND-1 study will inform the design and conduct of a large multicentre trial to compare the clinical and cost-effectiveness of the two treatments.

### Participants

Recruitment will take place in three secondary care sites in England: Derby Teaching Hospitals NHS Foundation Trust, Wrightington, Wigan and Leigh NHS Foundation Trust and Nottingham University Hospitals NHS Trust/Nottingham Treatment Centre.

Patients are eligible for the study if they are aged over 18 years, have one or more fingers with a Dupuytren’s contracture of more than 30° in the MCP and/or PIP joints, have a well-defined cord causing contracture, have had no previous surgery for Dupuytren’s contracture on the same hand, are willing to undergo either study procedure, and are able to complete the follow-up assessments. Exclusion criteria are Dupuytren’s contracture of the distal interphalangeal joints (DIP) only, having a planned dermofasciectomy or very limited fasciectomy (excision of up to 1 cm of cord segment), previous recruitment into the study, or a life expectancy of less than 3 years.

### Interventions

The two interventions are NF and LF. Following randomisation, participants will be placed on the NHS waiting list for their allocated treatment, which will be carried out by a competent surgeon (consultant or experienced trainee, or an inexperienced trainee under direct supervision of their trainer). The level of experience of the surgeon and key elements of the procedure, including start and end times and equipment used, will be recorded.

#### Needle fasciotomy

The procedure will be performed in a clinic room (not an operating theatre) equipped with a good ‘clinic room’ spotlight, wound swabs, a couch and possibly an arm board. The hand will be rested appropriately to allow full extension of the affected finger (to put the cord under tension). The cord must only be cut and no segment must be excised. A small amount of local anaesthetic is injected at the site of each point of division of the cord. The number of points along the cord at which division is attempted and choice of needle size is at the discretion of the surgeon. The use of a knife is permitted, but no tourniquet or other surgical instruments will be allowed. Either a multiple stabbing technique or a side-to-side cutting action can be used to divide the cord(s) in as many places as indicated.

#### Limited fasciectomy

The planned operation must be a LF (excision of more than 1 cm of cord), and not a very limited fasciectomy or a dermofasciectomy. This will be performed under either general or regional anaesthetic with the use of a tourniquet. The contracture will be exposed through a standard surgical incision. For contractures involving the MCP joint the Dupuytren’s cord must be excised proximally to at least the proximal margin of the transverse fibres of the palmar aponeurosis. Digital cords should be excised completely from their origin. In all cases the distal margin of the cord excision should be the insertion of the cord onto the flexor sheath (or other structure). Deviations from ‘limited fasciectomy’ (for example, a decision made during surgery based on unexpected operative findings to use a skin graft) will be recorded, as will the use of additional procedures such as release of a joint contracture.

If a patient presents with two or more fingers on the same hand that require treatment, then both/all fingers will be treated in the same manner (i.e. both/all with LF or both/all with NF). For any study outcomes that require reference to a single finger, the finger which the patient reports pre-operatively as causing the most trouble will be used.

### Outcomes

#### Patient-reported outcome measures (PROMs)

A range of outcome measures were identified as being potentially useful for a large-scale trial, one of the main goals for this study being to determine their appropriateness and usability. These included validated questionnaires on physical function and symptoms, changes in wellbeing and health outcomes. Participants in both study arms will be asked to complete the same series of PROMs at baseline and at 2-week, 6-week and 6-month follow-up as follows:Unité Rhumatologique des Affections de la Main (URAM) [19]Disabilities of the Arm, Shoulder and Hand Questionnaire (DASH) [20, 21]Part 2 of the Patient Evaluation Measure (PEM) [22]Measure Yourself Medical Outcome Profile (MYMOP) [23]EQ-5D-5 L descriptive system [24]

In addition, PEM will be completed on the day of surgery prior to treatment. This provides a check if symptoms have progressed differentially during this period, as waiting times from randomisation to surgery may differ for the two interventions.

#### Other clinical outcome measures

The following data will be collected at follow-up:Global Improvement Item [23] – self-completed by participants (to act as the anchor for the assessment of the performance of the PROMs)Complications following surgeryNHS resource use – patient-reported and obtained from medical recordsReturn to work/usual activities

The following objective outcomes will be measured at baseline and at 6-week and 6-month follow-up clinic visits:Grip strengthAngular measurement of finger straightness, with photographs taken for blinded assessment

Standardised photographs will be taken using the Nottingham Dupuytren’s Assessor which has been developed for the purposes of the study.

### Sample size

As this is a feasibility study, a formal sample size calculation is not appropriate. It is anticipated that 50–85 participants will be recruited across the three sites. One of the primary aims of this feasibility study is to estimate response to invitation, eligibility, consent, randomisation and follow-up. Based on an expected total number to be invited of 400, estimated margins of error for these proportions will range between 5 and 13%.

### Recruitment and follow-up

Recruitment will take place from November 2015 to September 2016. Participants will be recruited from secondary care clinics at three sites in England. Patients who are referred by their general practitioner (GP) to the hand surgery outpatient clinic will be sent a short Patient Information Leaflet before their appointment which will explain Dupuytren’s contracture of the fingers and that they may be invited to participate in the study during their clinic visit. The leaflet will also explain that they may be asked for permission to audio-record consultations with the surgeon and research nurse/assistant during the clinic visit. These audio-recordings form part of the QRI and will help to understand and optimise the recruitment process. Trial posters will also be displayed in waiting areas in recruiting clinics to raise awareness of the study.

Following randomisation, participants are placed on the NHS waiting list for their allocated treatment, and each participant is followed up for 6 months following their surgery. At the end of the follow-up period information from the medical records will be extracted to record any outpatient appointments, outpatient procedures, emergency department visits or inpatient admissions related to the study hand in the 6 months after the initial procedure. Participants may be invited to take part in qualitative interviews up to 6 months after treatment.

Upon completion of all trial visits and questionnaires, participants will receive an end-of-study letter accompanied by an Information Sheet thanking them and informing them that their participation in the study is complete. Details of the data collection schedule are summarised (see Fig. 2).

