### Statistical analyses

The analysis and reporting of the trial will be in accordance with extensions of the Consolidated Standards of Reporting Trials (CONSORT) Guidelines for Pilot and Feasibility Trials [25] and Non-Pharmacologic Treatment Interventions [26].

Continuous variables will be summarised in terms of the mean, standard deviation, median, lower and upper quartiles, minimum, maximum and number of observations. Categorical variables will be summarised in terms of frequency counts and percentages. A CONSORT flow diagram showing the numbers of people approached, eligible, recruited and randomised (with reasons for exclusions) will be produced. Recruitment rates at the start and end (after modification of the recruitment method based on the qualitative studies) of the recruitment phase of the study will be compared. Numbers and characteristics of participants recruited will be summarised using appropriate descriptive statistics and compared with patients who were eligible but not randomised. Completeness of data collection will be compared between trial arms. A Statistical Analysis Plan (SAP) will be agreed before data are unblinded.

We will ‘micro-cost’ [27] NF and LF by combining resource use with unit costs provided by the hospital finance departments. Standard unit costs will be used to estimate the NHS costs of care in the 6 months post procedure [28, 29]. Descriptive summaries of NHS cost data and return to work/usual activities at each follow-up time point will be presented.

Minimum clinically important effects for each PROM will be estimated using three anchor-based responsiveness statistics: (1) standardised response mean (SRM), (2) effect size (ES) and (3) Guyatt’s Responsiveness Index (GRI). This analysis will guide the choice of PROM for use in a definitive trial of treatment of Dupuytren’s disease, along with participant ranking of the different PROMs.

Improvements in the ability to extend the finger(s) after surgery will be compared with these responsiveness indices to investigate its use as a surrogate measure of hand function and calculate its minimum clinically important difference (MCID).

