## Discussion

The current lack of robust evidence on treatment for Dupuytren’s contractures of the fingers means that the choice of treatment mainly depends on surgeon and patient preferences. A comparison of NF with LF has been identified as an important research question for both surgeons and patients [5]. However, it is uncertain whether surgeons will be willing to recruit, and whether patients will be willing to be randomised to such a study of two treatments which have very different patient pathways. Social circumstances, such as self-employment, duties as a carer for a relative and the financial burden of prolonged sick leave, may all influence each patient’s treatment preference, as may the desire for a straight, aesthetically satisfying finger, or to minimise the risk of needing further surgery in the future. Although some surgeons are confident with NF and willing to treat patients with well-defined cords causing either MCP or PIP joint contractures, others are reluctant to treat PIP contractures as they are concerned about damaging a digital nerve and also may not consider NF successful in treating these particular contractures. This is despite a large series reporting low incidences of digital nerve damage with NF [33] and a general acceptance that all procedures are less good at straightening PIP contractures than MCP ones. From a patient’s perspective, the options of NF and LF offer very different short- and long-term benefits, and thus many may find one treatment option suits their lifestyle much better than the other. The integrated qualitative and QRI component of the HAND-1 study will provide fundamental insights into the feasibility and design of a main trial.

The assessment of outcome of Dupuytren’s treatment with PROMs is in its infancy, and success or failure of the treatment has previously been determined by the amount of angular correction (straightening) of the flexed finger and the subsequent amount of recurrent angular deformity occurring over a pre-set time period, regardless of whether this results in the patient wishing to undergo further treatment to straighten the finger again. This is particularly unsatisfactory as the relationship between hand and finger function and joint-angle deformity is controversial.

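### The records extraction and the costing of NHS care both start at the procedure, so hospital contacts between randomisation and surgery fall outside them, and no other collection of them is described

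*Protocol article*

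**What the plan says.** All references are to the protocol article.

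- **Records extraction (Recruitment and follow-up).** At the end of follow-up, medical records are searched for clinic attendances and procedures, emergency visits and admissions "related to the study hand in the 6 months after the initial procedure".
- **Costing of care (Statistical analyses).** "Standard unit costs will be used to estimate the NHS costs of care in the 6 months post procedure".
- **Costing of the procedures (Statistical analyses; Interventions).** NF and LF are micro-costed "by combining resource use with unit costs provided by the hospital finance departments". On the recording side, "key elements of the procedure, including start and end times and equipment used, will be recorded".
- **Patient-reported resource use (Other clinical outcome measures).** This is one of the items collected at follow-up. The period that it asks about is not stated.
- **Clock (Recruitment and follow-up).** After randomisation, "participants are placed on the NHS waiting list for their allocated treatment", and "each participant is followed up for 6 months following their surgery".
- **Differences between the arms before surgery.** The PROMs section says that "waiting times from randomisation to surgery may differ for the two interventions" and adds a day-of-surgery PEM for that reason. The Discussion speaks of "two treatments which have very different patient pathways".
- **Participants without the allocated procedure (Data collection, management and analysis).** They stay in follow-up unless they withdraw completely.

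**The concern.** In a randomised comparison, resource use belongs to an arm from the moment of allocation. Here the allocation is disclosed at randomisation and the participant then waits for that specific treatment. A study-hand contact during the wait may therefore be a consequence of the allocation, yet both windows open only at the procedure.

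The article recognises the problem for symptoms. Because waits may differ by arm, it adds a PEM on the day of surgery. It describes no matching step for resource use.

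The study is meant to inform a trial of clinical and cost-effectiveness, and one of its objectives is to evaluate the resource-use questionnaires. If the collection that is piloted leaves out part of the randomised pathway, the definitive trial could inherit the gap.

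**Working it through.** No stated figure is at issue and there is nothing to recompute. The check sets the described data sources against the participant's timeline.

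| Period | Records extraction | Cost-of-care estimate | Micro-cost | Patient-reported resource use |
|---|---|---|---|---|
| Randomisation to day of surgery | Outside | Outside | Boundary not stated | Collected at follow-up; recall period not stated |
| Procedure | – | – | Yes | – |
| 6 months after the procedure | Inside | Inside | – | Yes |

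1. *Where the windows open.* Both the extraction and the cost-of-care sentences name the procedure as the start. This is stated, not inferred.

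2. *Whether another source covers the wait.* Two sources might. The micro-cost could include pre-operative work, but the items named for recording are elements of the procedure itself. The list is introduced as non-exhaustive, so it does not settle the matter. The patient-reported items could look back before surgery, but nothing says that they do. The supportable statement is that no collection of pre-surgery contacts is described.

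3. *Whether the interval matters.* Participants go onto an NHS waiting list of unstated length. Table 1 provides postal follow-up for participants whose wait leaves no time for a 6-month visit within the study period, so the interval cannot be assumed negligible for everyone.

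4. *Whether the arms could differ.* LF takes place in an operating theatre under general or regional anaesthesia, and the Background describes it as typically a day-case admission. NF uses local anaesthetic in a clinic room. The Discussion calls the pathways very different as a fact. Different waits are stated only as a possibility.

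5. *Participants with no procedure.* The extraction is anchored on the initial procedure, not the allocated one. Someone who receives the other treatment therefore has a defined window. Someone who remains in follow-up and has neither treatment has no start date for the records or costing window.

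6. *Size.* An estimate would need the number of study-hand contacts per participant before surgery in each arm, and their unit costs. The article gives neither, and gives no waiting times. Any figure would be arithmetic on guesses, so none is offered.

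**The case against.** The strongest reply is that starting at the procedure is coherent. All follow-up runs from surgery, so each treated participant is costed over the same 6 months and alongside the outcomes. A window that starts at randomisation would vary in length with the wait. This stands as a reason to keep the 6-month summary. It is not a reason to leave the wait uncollected, because the pre-procedure part can be reported as its own line.

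The second reply is that costs are only summarised descriptively, no cost-effectiveness estimate is planned, and the economic objective is to evaluate questionnaires. This also stands. It limits the consequence for this study's own results and moves the weight of the point to what is carried into the definitive trial.

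Three stronger readings are tempting and are not supported:

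- *That pre-surgery contacts are never collected.* A reader might infer this, but the micro-costing boundary and the questionnaire recall period are not stated. The schedule in Fig. 2 could not be seen for this review and should be checked.
- *That the windows understate the LF cost and bias the LF–NF difference in one direction.* More pre-operative contacts with LF would be a reasonable expectation from the two settings. However, the article reports no pre-operative assessments, rebooked admissions or contact rates for either arm, so neither direction nor size can be shown.
- *That a participant with no procedure contributes no cost at all.* Such a participant stays in follow-up, where resource use is also patient-reported. What is missing is a defined records and costing window.

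**Conclusion.** The point holds in a limited form. The records extraction and the cost-of-care estimate exclude the period from randomisation to surgery by their own wording. No other collection of study-hand contacts in that period is described, although the article states that the pathways differ greatly and that the waits may differ. Participants followed up without any procedure have no defined window.

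The size and direction of any omission are unknown. The conclusion assumes that neither Fig. 2 nor the full protocol provides a pre-surgery resource-use item. If one of them does, the remedy reduces to saying so and defining the window for participants with no procedure. Label: cheap improvement. The benefit lies mainly in piloting a complete resource-use collection for the definitive trial.

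**What to change.** 1. Extract study-hand contacts from randomisation to 6 months after the initial procedure.
2. Report the part before the procedure as a separate descriptive line by arm, next to the micro-cost and the post-procedure cost. State the micro-costing boundary so that nothing already in it is counted twice.
3. Leave the 6-month post-procedure summary exactly as planned.
4. For participants who have no procedure, set a fixed window that starts at randomisation, with its length decided before the data are unblinded.

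The same records are already opened once at the end of follow-up, for an anticipated 50–85 participants. The cost is reading back to the randomisation date and adding a section to the extraction form, which means slightly more extraction time per participant.
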